### Statistical analysis

The primary endpoint is the repeated measurements of MDAS over time. Differences in the MDAS trajectories between the treatment groups will be analysed by a mixed linear model. In addition we will, as a secondary endpoint, compare the time to resolution of delirium as measured by DSM-5. The Kaplan Meier method and the logrank test will be applied. In addition a Cox proportional hazards model will be applied to estimate hazard ratios. The additional different secondary endpoints will be analysed by t-tests when variables are continuous and by chi-square tests when variables are categorical. Patient survival will be compared between groups by the logrank test and Cox proportional hazards model.

For the comparison of the MDAS trajectories no adjustment for multiplicity will be applied. If a statistically significant difference between the MDAS trajectories is demonstrated, analyses of secondary endpoints will be performed without any formal adjustment for multiplicity. If any conclusion on efficacy is to be drawn based on a secondary endpoint only, a simple Bonferroni adjustment (dividing the 5% level with the actual number of tests performed) will be applied. If the use of additional antipsychotics differs between treatment groups, the amount calculated as haloperidol equivalents [68] will be included in the statistical model.

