### Safety review

A safety review will be done after we have recruited 20 patients (10 placebo and 10 clonidine). Recruitment of the additional 80 patients will be halted until we have made an assessment of the serum concentration levels, pharmacokinetics and -dynamics (the haemodynamic response) in these initial 20 patients. These data will then guide further dosage for the subsequent 80 patients. We are aiming for serum concentration levels between 0.3 and 0.7 ng/ml, but may accept a small number of single measures above this range. Blood samples for serum concentration measurement will be taken 3 hours after the patient has taken the study drug (each time) on day 1 and just before administration of study drug between 0800 and 0900 on day 2. The serum concentration levels and pharmacodynamic responses will be assessed by an independent Data Monitoring Committee. The determination of the further dosage plan will thus be based on both pharmacokinetics/serum concentration levels and the individual patients´ haemodynamic responses. The further dosage plan will be approved by The Norwegian Medicines Agency.

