### Sample size, statistical power and statistical analysis

Based on the expected number of patients fulfilling the inclusion criteria within 36 months a sample size of n = 100 was chosen. Inclusion of 100 patients would lead to a power of only 71% to detect an absolute treatment difference of 25% in proportion recovered according to DSM-% (40% vs 65%). Correspondingly, using MDAS at one single point in time as the response measure would lead to approximately 80% power assuming a standard deviation of 9 and a difference in mean MDAS score of 5. Thus, analyzing treatment efficacy at only one point in time would lead to low power. An analysis of repeated measurements will reduce random variability and thereby increase power. The primary analysis is therefore a mixed linear model taking all MDAS measurements into account.

The expected efficiency gain is difficult to estimate precisely, but assuming a standard deviation of 9 on the MDAS and a correlation between measurements of r = 0.5, the power would be around 95% to detect a mean MDAS difference of 5 or a power of 80% to detect a mean difference of 3.5 between groups.

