## Discussion

Delirium is a severe and common condition among acute hospitalised elderly patients, and the options for pharmacological treatment are sparse. To our knowledge, no randomised placebo controlled trial investigating treatment of delirium with clonidine or other alpha-2-adrenoreceptor agonists has yet been done in non-critically ill medical patients. It has been recommended [85,86] that future studies on pharmacological treatment of delirium should have less restrictive exclusion criteria, in order to avoid low external validity. Further, future studies should ensure stratification according to known underlying risk factors for delirium. The trials should then have a true placebo arm and use validated instruments for delirium assessments. We have planned this trial according to these guidelines.

The results of our study will be more clinically relevant if the medication is easy and safe to administer to patients in a general ward, without the need for invasive monitoring. Frail and demented patients are more prone to develop delirium, and the treatment regimen should be feasible for this large group of patients. Thus, it is important that the exclusion criteria are not too strict, and we will therefore include patients with dementia and patients from nursing homes in this trial.

Delirium is a clinical diagnosis, based on history, information from proxies, mental status examination and evaluation of an underlying medical cause. There is no single simple test, neither psychometric nor physiological, to ascertain delirium. We have described the procedure that we will use to make the final diagnosis according to the DSM-5 criteria. All assessments of delirium will be made by the investigators (geriatricians trained in delirium evaluation) during weekdays, and by geriatricians on call in the weekends.

The primary outcome in this study is the trajectory of delirium, measured daily by MDAS. Due to features common in studies of delirium (small sample sizes, sample attrition, fluctuation course of the disease and spontaneous recovery), techniques that use all available data and take a global (as opposed to end-of-trial) perspective are preferred [87]. Using longitudinal trajectories as the main outcome will almost always have greater power than end-of-trial analyses [87-89], as well as reducing the problem with missing data.

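### The primary test is worded as a difference in MDAS trajectories, but the stated power is for a mean MDAS difference, and the tested contrast is not named

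*Protocol article*

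**What the plan says.** All references are to the protocol article. Under Primary endpoint, the endpoint is the delirium trajectory, meaning MDAS severity over time. Under Statistical analysis, "Differences in the MDAS trajectories between the treatment groups will be analysed by a mixed linear model". The same section adds "For the comparison of the MDAS trajectories no adjustment for multiplicity will be applied", and lets secondary endpoints be analysed without formal adjustment once the trajectory difference is significant.

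Under Sample size, statistical power and statistical analysis, the mixed model is chosen because repeated measurements reduce random variability. Its power is then given in two forms. The first is "the power would be around 95% to detect a mean MDAS difference of 5"; the second is 80% for a difference of 3.5. Both figures were obtained by "assuming a standard deviation of 9 on the MDAS and a correlation between measurements of r = 0.5". The Discussion prefers a global view to an end-of-trial one, and lists "fluctuation course of the disease and spontaneous recovery" among the common features of delirium studies.

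No section says whether the tested term is a group effect averaged over time, a difference in slopes, or a joint group-by-day interaction.

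**The concern.** In a mixed model, a difference in trajectories is often tested as a group-by-time term, and a difference in means as a group effect averaged over time. The two can have very different power on the same data. The article words its hypothesis in the first way and justifies its size in the second.

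This is the only primary test, and it also decides whether the secondary endpoints are read without adjustment. If an analyst took the wording at face value and tested a linear slope difference, the quoted power would not describe the test. Because recovery is expected in both arms, the gap between them may open early and then close, and a straight-line slope summarises that shape poorly.

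**Working it through.** **Inputs.** Total size: "a sample size of n = 100 was chosen". I assume 50 per arm; equal allocation is implied by "A safety review will be done after we have recruited 20 patients (10 placebo and 10 clonidine" but is not stated for the whole trial. Alpha is 5% ("dividing the 5% level with the actual number of tests performed"), taken as two-sided. SD is 9 and r is 0.5, with compound symmetry assumed. The number of measures behind the power figure is not given; I assume 7 daily measures, t = 0 to 6, with t = 0 as baseline, and complete data. Power is Φ(effect/SE − 1.96); the opposite tail matters only when the effect is near zero.

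**1. The plan's own figures.**
- One time point: SE = 9 × √(2/50) = 1.80; 5/1.80 = 2.78; power 79%. The plan says about 80%.
- Mean of k measures: SE = 9 × √[(1 + (k − 1) × 0.5)/k] × √(2/50). For k = 7, SE = 1.361 and power at 5 points is 96%. For k = 6 (post-baseline only), SE = 1.375 and power is 95%. The stated 95% is reproduced as a time-averaged group difference.
- At 3.5 points with k = 6: 3.5/1.375 = 2.55; power 72%, not the stated 80%. With unlimited measures the SE falls only to 9 × √0.5 × √(2/50) = 1.273, which gives about 79%.

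**2. Linear group-by-time slope, same inputs.** The within-patient residual variance is 81 × (1 − 0.5) = 40.5, and Sxx for t = 0 to 6 is 28. SE = √(40.5/28 × 2/50) = 0.241 per day.

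| Shape of the gap between arms | Slope difference per day | Slope power |
|---|---|---|
| 5 at every measure, including the first | 0 | 5% (alpha) |
| 0 at baseline, then 5 | 5 × 3/28 = 0.536 | 61% |
| 0 at baseline, then 3.5 | 3.5 × 3/28 = 0.375 | 34% |
| Growing linearly, averaging 5 after baseline | 5/3.5 = 1.43 | above 99% |

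**3. Joint group-by-day (omnibus) test.** Noncentrality is Σ(d − d̄)²/(40.5 × 2/50) on 6 degrees of freedom, where d is the gap on each day. For the gap that opens to 5 after baseline this is 21.43/1.62 = 13.2, giving 79% power. For a constant gap it is 0, giving 5%.

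**4. Early separation, then convergence.** These curves are my assumption; the article gives no recovery rates. MDAS falls from 18 as 18·exp(−t/5) on placebo and 18·exp(−t/2) on clonidine.
- t = 0 to 6: the post-baseline mean gap is 5.1 (mean contrast 96%). The slope has the correct sign, with 68% power. The omnibus test has about 86%.
- t = 0 to 13: the mean gap after baseline is still 3.7 in favour of clonidine (79%). The slope difference is 0.19 per day in favour of placebo; with Sxx = 227.5 and SE = 0.084 it is significant in that direction about 60% of the time. The omnibus test has about 95%.

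**5. Baseline adjustment.** The variance of the six-measure mean is 1.375² × 25 = 47.25. Its covariance with baseline is 40.5, so the adjusted variance is 47.25 − 40.5²/81 = 27. SE = √(27 × 2/50) = 1.039. At 3.5 points, 3.5/1.039 = 3.37 and power is 92%.

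**The case against.** The strongest reply is that the article never mentions a slope, an interaction or a group-by-time term. It describes the endpoint as repeated MDAS measurements, argues from reduced random variability, prefers a global view, and gives its only effect size for this model as a mean difference. A time-averaged group effect fits all of this, and on that reading test and power agree. The exact model term is also normally settled in an analysis plan or full protocol, neither of which is shown.

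Most of that stands, and it limits the point. Three stronger readings are tempting and are not supported:

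- *That the trial has committed to an underpowered test.* It has left the contrast open. Nor is low power a general property of group-by-time tests: the slope exceeds 99% for a steadily growing gap, and the omnibus test reaches 79% to 95% in the early-opening and converging scenarios above.
- *That a real benefit would appear with the wrong sign.* Under these curves that needs a linear slope and 14 complete daily measures. Over 7 days the sign is right. Under Study design, assessment stops at discharge, so 14 complete days for every patient is unlikely. An omnibus test has no direction.
- *That the absence of a multiplicity adjustment gives two chances to claim success.* The sentence describes one primary comparison, which needs no adjustment. Nothing allows a claim on either of two tests.

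What the reply does not remove is visible in the article itself: the hypothesis is worded as one quantity, the power is stated for another, and no sentence connects them.

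**Conclusion.** The point holds as a mismatch that needs settling, not as a demonstrated loss of power. The stated 95% at 5 points is correct for a time-averaged group difference and cannot be carried over to every reading of a trajectory difference. For a linear slope over 7 daily measures, power runs from 5% to above 99% according to the shape of the gap, with 61% for a 5-point gap that opens after baseline. A linear slope can also mislead if the arms separate early and then converge, depending on the window and the curves assumed.

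These figures rest on equal arms, compound symmetry, a two-sided 5% level, 7 measures and no missing data. The point is worth acting on because this test governs how the secondary endpoints are read, and because the unadjusted mean contrast has only about 72% power at 3.5 points, where the article claims 80%.

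**What to change.** Name one primary contrast: the treatment difference in mean MDAS averaged over the post-baseline treatment days (days 2 to 7 if day 1 is baseline), from a mixed model with day as a categorical factor and baseline MDAS as a covariate. Report group-by-day as descriptive. This is the quantity for which the power was computed, and baseline adjustment lowers the SE from 1.375 to 1.039. Restate the power for the adjusted contrast: about 92% at 3.5 points under the plan's SD and correlation.

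If a slope or interaction test is what is intended, say so and restate the power for that test under a stated shape of the treatment gap.

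The cost is a change of wording and a revised power statement. No extra patients or measurements are needed, because MDAS is already assessed for all included patients.

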### Randomisation and blinding

The randomisation is based on computer-generated random numbers, and will be carried out by a statistician. The randomisation schedule will be distributed to the producer of the study medication, and capsules made accordingly. The randomisation will be stratified with respect to whether or not the patient was admitted from a nursing home, in order to balance the groups with respect to pre-admission cognitive decline, independence and comorbidity, all important prognostic factors.

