### Data collection

Demographic data, medical history, information regarding the acute underlying medical disease(s), drug use and proxy information will be collected during the hospital stay. Once included in the study, patients will be visited daily for efficacy and safety evaluations by the study physicians (geriatricians) or by the consultant on-call during the weekend.

We will assess pre-existent functional and cognitive status by asking the patient’s primary caregiver (the best available source) to complete questionnaires to assess the patient´s functional and cognitive state two weeks prior to hospital admission. Functional status will be assessed using the Barthel ADL Index [69] and the Nottingham Extended ADL Index (NEADL) [70]. To ascertain prior long-term cognitive decline we will use the Informant Questionnaire on Cognitive Decline in the Elderly (IQCODE) [71] and the Clinical Dementia Rating Scale (CDR) [72]. The Mini-Mental State Evaluation – Norwegian version (MMSE-NR) [73,74] will be performed at baseline and at discharge for the purposes of general cognitive screening. The Cornell Depression Scale [75,76] is based on proxy information and will be used to evaluate the degree of depressive symptoms.

Grip strength of the dominant hand will be measured using hand-held dynamometry once during the hospital stay and at follow-up after 4 months. The severity and number of comorbidities will be scored using the Cumulative Illness Rating Scale (CIRS) [77]. The level of physiological disturbance will be assessed by using Acute Physiology and Chronic Health Evaluation II (APACHE II) [78], the version utilising venous bicarbonate rather than arterial blood gases. Body Mass Index is registered as a marker of nutritional status.

We will use the algorithm described in the section above and in Table 4 to diagnose delirium (or subsyndromal delirium) according to the DSM-5 criteria.

We will also collect data about patient distress, using items from The Checklist of Nonverbal Pain Indicators (CNPI) [79]. Possible and suggestive causes of delirium are registered in each case at discharge.

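### Secondary endpoints are assigned unadjusted tests although randomisation is stratified by nursing home and pre-admission scores are collected

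*Protocol article*

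**What the plan says.** **Randomisation.** Under Randomisation and blinding: "The randomisation will be stratified with respect to whether or not the patient was admitted from a nursing home". The stated purpose is balance on pre-admission cognitive decline, "independence and comorbidity, all important prognostic factors".

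**Baseline data.** Under Data collection, a caregiver describes the patient's state two weeks before admission: "Functional status will be assessed using the Barthel ADL Index", together with NEADL, and IQCODE and CDR for cognition. Table 2 and Follow-up assessments place the same four instruments at 4 months.

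**Secondary tests.** Under Statistical analysis: "The additional different secondary endpoints will be analysed by t-tests when variables are continuous and by chi-square tests when variables are categorical". For time to resolution, the main secondary endpoint: "The Kaplan Meier method and the logrank test will be applied". A Cox model is added, with covariates not listed. Survival gets the same pair, logrank and Cox.

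**Primary test.** "Differences in the MDAS trajectories between the treatment groups will be analysed by a mixed linear model". The sample size section adds: "The primary analysis is therefore a mixed linear model taking all MDAS measurements into account". Fixed effects are not listed. The only covariate named anywhere in the analysis section is antipsychotic use in haloperidol equivalents, and only if use differs between arms.

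**The concern.** The design treats nursing-home residence as prognostic, and the data collection supplies a like-for-like earlier value for four of the 4-month scales. The tests named for the secondary endpoints use neither. A t-test or chi-square test has no place for a covariate, so this is a choice of method that the article makes, not detail left to a fuller document.

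Two things are at stake. Unexplained between-patient variation stays in the standard error, and a chance difference between arms in pre-admission function or cognition stays in the 4-month estimate. After stratified randomisation, a test that ignores the stratum is also slightly conservative. The sample of 100 was set by expected recruitment, so precision cannot be bought with more patients. Although the Discussion calls the secondary objectives exploratory, Statistical analysis allows an efficacy conclusion from a secondary endpoint alone under a Bonferroni correction, where lost precision costs more.

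**Working it through.** **Inputs from the article.** N = 100; SD 9, difference 5 and correlation r = 0.5 on MDAS; 5% level.

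**Assumptions.** Two-sided test; 50 per arm (the first 20 patients split 10 and 10); no dropout; correlation ρ of 0.5 to 0.7 between pre-admission and 4-month scores, with 0.3 shown as a low case; nursing-home share q of 10% to 50%; shift D between strata of 0.3 to 0.8 within-stratum SD.

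**1. The plan's own figure.** Power = Φ(δ / (SD·√(2/n)) − 1.96). Here 9·√(2/50) = 1.80 and 5/1.80 = 2.78, so power = Φ(0.82) = 79.3%. The article says approximately 80%, so its single-time-point figure is reproduced and is that of an unadjusted comparison.

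**2. Adjusting for an earlier value of the same scale.** ANCOVA multiplies the variance by 1 − ρ², whatever the number of patients. The article gives no effect size for the 4-month scales, so the power column borrows the MDAS effect (5/9 SD) as an illustration.

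| ρ | Variance cut (ρ²) | Power, 50 per arm | Per arm to match unadjusted 50 |
|---|---|---|---|
| 0 (t-test) | 0% | 79.3% | 50 |
| 0.3 | 9% | 82.9% | 46 |
| 0.5 | 25% | 89.4% | 38 |
| 0.7 | 49% | 97.3% | 26 |

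At ρ = 0.5, for example: 2.78/√0.75 = 3.21, and Φ(3.21 − 1.96) = 89.4%.

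**3. The stratum alone.** R² = q(1 − q)D² / (1 + q(1 − q)D²).

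- Low end, q = 0.1 and D = 0.3: 0.0081/1.0081 = 0.8%; power 79.6%.
- High end, q = 0.5 and D = 0.8: 0.16/1.16 = 13.8%; power 84.9%.

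The gain over 79.3% is therefore 0.3 to 5.6 points. If the stratum is balanced but ignored, the true type I error is about 2(1 − Φ(1.96/√(1 − R²))), or 4.9% down to 3.5%.

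**4. Under a Bonferroni route.** The number of tests is not fixed. With 14 (the secondary rows of Table 2, for illustration) the level is 0.05/14 = 0.0036 and the critical value 2.91. Power for the same effect is Φ(2.78 − 2.91), about 45%, unadjusted, and Φ(3.21 − 2.91), about 62%, with ANCOVA at ρ = 0.5.

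**5. Which endpoints gain what.** Barthel, NEADL, IQCODE and CDR have a like-for-like earlier value and can gain as in step 2. Length of stay, survival and rescue medication have none, and can gain only as in step 3.

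**The case against.** The strongest reply is that this is not an error. Unadjusted tests are valid after stratified randomisation, the Discussion calls the secondary objectives exploratory and the sample too small for conclusive results on them, and the stratum is worth little. The Cox models named beside the logrank tests can carry the stratum, since their covariates are left open. The correlation of 0.5 to 0.7 is assumed. All of this stands. It limits the point to efficiency and puts most of the gain in four scales. It does not remove the point, because the t-test and chi-square test are named and cannot be extended.

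A reader might also infer that the primary analysis ignores baseline MDAS and the stratum, at a large cost. With r = 0.5 and an assumed five post-baseline values, the variance factor for the mean score is 0.5 + 0.5/5 = 0.60 unadjusted and 0.60 − 0.25 = 0.35 with baseline as covariate. That is a 42% cut, with power for 3.5 points rising from 71% to 91%. The arithmetic is right, but the article does not support the premise:

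- It neither lists nor excludes fixed effects. A model with a common baseline mean is itself a mixed linear model using every MDAS value, and a covariate list is commonly left to the fuller document.
- The endpoint is a trajectory. For a slope over the same five days under compound symmetry, the per-patient variance is 0.5/10 = 0.05 SD² with or without baseline as a main-effect covariate, so the 42% need not carry over.
- The stated power does not settle the matter. About 95% at 5 points fits five to seven unadjusted values (94.8% to 95.7%), but 80% at 3.5 points exceeds what unlimited unadjusted values give (78.5%).

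**Conclusion.** The point holds for the secondary endpoints. The article assigns them t-tests, chi-square tests and a logrank test without named strata, and so leaves unused a stratification factor that it calls prognostic and pre-admission scores that it collects.

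The size is a variance reduction of 25% to 49% for 4-month Barthel, NEADL, IQCODE and CDR, if the correlation with the pre-admission value is 0.5 to 0.7. The stratum alone adds about 0 to 6 power points under the assumed shares and shifts. It would overstate the case to say that the trial gives up much of its precision. The unadjusted tests are valid and slightly conservative, and the trial's power rests on the primary model, for which no loss can be shown. This is an improvement at almost no cost, plus one request to make the primary model explicit.

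**What to change.** Amend the secondary analyses before unblinding:

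- **4-month Barthel, NEADL, IQCODE and CDR:** ANCOVA on the pre-admission value plus the nursing-home stratum, in place of t-tests.
- **Time to resolution and survival:** logrank and Cox analyses stratified by nursing home.
- **Binary endpoints:** Mantel-Haenszel by stratum, or logistic regression with the stratum as a term.
- **Continuous endpoints without an earlier value, such as length of stay:** a linear model with treatment and stratum.
- **Primary model:** state that it includes the nursing-home stratum and baseline MDAS, with baseline either as a covariate or as an outcome with a mean common to both arms.

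The cost is wording and one or two degrees of freedom per model. No new data are needed. The plan should say how a missing pre-admission questionnaire is handled, so that patients are not lost from the 4-month analysis. Naming the covariates in advance also prevents their being chosen after the results are known.

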**Primary**	
Delirium trajectory	MDAS
**Secondary** (also with subanalyses for subsyndromal delirium and hypoactive/hyperactive/mixed delirium)	
Time-to-first delirium resolution	DSM-5
Incidence of “full-scale” delirium	DSM-5
Severity of delirium	MDAS, OSLA
Delirium subtype	MDAS, OSLA, DelApp
Use of “rescue medication”/additional drugs (as other sedatives, analgetics and antipsychotics)	Registration of use of all medication
Length of hospital stay	Registrations
Patient distress	Checklist of Nonverbal Pain Indicators
Cognitive function in follow-up after 4 months	MMSE-NR, Clock drawing test, Ten-words memory test, Trial making test A and B, IQCODE, CDR
Independence in follow-up after 4 months	Barthel ADL, NEADL
Pharmacokinetic response to clonidine	Serum drug concentrations
Pharmacodynamic response to clonidine	BP, HR, ECG, RASS, OSLA, symptoms of bradycardia, orthostatic hypotension or other side-effects
Biomarkers	Blood samples
Institutionalisation	Registrations
Survival	Registrations

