It is important to determine whether clonidine will have a differential impact on hyperactive versus hypoactive subtypes of delirium, or even only on certain features of delirium (e.g. inattention). The sample size of this study is too small to give conclusive results regarding secondary endpoints. However, these secondary objectives are exploratory and may generate new hypotheses and give direction for future studies.

Any positive results of clonidine on delirium symptoms will also contribute to the discussion about the underlying pathophysiology and the role of the autonomic nervous system in delirium. Studies of dexmedetomidine have showed promising results with respect to delirium duration and severity in the intensive care unit patients, but it is still uncertain weather this is an opioid- and benzodiazepine-sparing effect alone or if dexmedetomidine has truly delirium modulating effects [36,37]. Any positive effect of clonidine compared to placebo may indicate that the sympathetic nervous system and related stress systems are involved in the underlying pathophysiology of delirium.

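### The primary takes the full 5% and a secondary-only efficacy claim gets a further 5%, so the false-claim rate can reach 10%; the Discussion says secondaries cannot be conclusive

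*Protocol article*

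**What the plan says.** The Statistical analysis section sets three rules.

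- Primary: "For the comparison of the MDAS trajectories no adjustment for multiplicity will be applied". It is tested at the full 5%.
- If the primary is significant: "analyses of secondary endpoints will be performed without any formal adjustment for multiplicity".
- Secondary-only route: "If any conclusion on efficacy is to be drawn based on a secondary endpoint only", then "a simple Bonferroni adjustment (dividing the 5% level with the actual number of tests performed) will be applied".

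Table 2 lists 14 secondary rows, several with more than one instrument, "also with subanalyses for subsyndromal delirium and hypoactive/hyperactive/mixed delirium". The text does not say whether the primary counts in the divisor.

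The Discussion gives the secondaries a different standing: "The sample size of this study is too small to give conclusive results regarding secondary endpoints". It continues: "However, these secondary objectives are exploratory and may generate new hypotheses and give direction for future studies".

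**The concern.** A conclusion resting only on a secondary endpoint is one reached without a significant primary. By then the MDAS test has used the whole 5%. The third rule gives the secondary family another 5%, with nothing taken from the primary to pay for it. The trial thus has two separate routes to an efficacy conclusion, each controlled at 5%, and no control over the two together.

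What is at stake is how a negative trial may be reported. If the MDAS comparison fails, the rule still lets one secondary endpoint support a statement that clonidine works, at an overall error rate that the protocol does not state. The Discussion says that the trial cannot give that kind of answer.

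**Working it through.** **Inputs.** The primary level is 5% and each secondary on the secondary-only route is tested at 5%/k (Statistical analysis). The number of secondary tests k is not fixed, so k = 1 to 30 was tried, with k = 14 (the rows of Table 2) as the reference. The sample is 100 patients (Sample size section), taken as 50 per arm because the Safety review splits its first 20 patients 10 and 10.

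**The protocol's own figures.** It states no overall false-positive rate. Its powers were reproduced to confirm the test level, since sidedness is not stated.

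- Recovery 40% vs 65%, 50 per arm, two-sided 5%, pooled null variance: SE under the null = √(2 × 0.525 × 0.475/50) = 0.0999; SE under the alternative = √(0.4 × 0.6/50 + 0.65 × 0.35/50) = 0.0967. Power = Φ((0.25 − 1.96 × 0.0999)/0.0967) = 71.3%, against 71% stated.
- Single-time MDAS, difference 5, SD 9: Φ(5/(9√(2/50)) − 1.96) = Φ(2.778 − 1.960) = 79.3%, against approximately 80% stated.

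A two-sided 5% level therefore fits the document.

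**Upper bound under the global null.** 5% + k × (5%/k) = 10% for any k.

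**Independent tests.** Rate = 1 − 0.95 × (1 − 0.05/k)^k. If the primary is counted in the divisor, replace 0.05/k by 0.05/(k + 1).

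| k | divisor k | divisor k + 1 |
|---|---|---|
| 1 | 9.75% | 7.4% |
| 5 | 9.66% | 8.9% |
| 14 | 9.64% | 9.3% |
| 30 | 9.64% | 9.5% |

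Worked for k = 14: (1 − 0.05/14)^14 = 0.9511; 1 − 0.95 × 0.9511 = 9.64%.

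**Correlated tests.** These come from multivariate-normal simulation with 400,000 draws, k = 14 and divisor k. The correlations are assumptions.

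| Assumed correlation | False efficacy claim |
|---|---|
| 0.3 throughout | 8.9% |
| 0.5 throughout | 7.8% |
| 0.7 throughout | 6.4% |
| 0.9 throughout | 5.1% |
| MDAS and 3–4 delirium endpoints at 0.7–0.8, the rest at 0.1–0.3 | 8.2–8.9% |

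The mixed pattern seems the most plausible. DSM-5 resolution and severity should move with MDAS, while length of stay, institutionalisation and survival should do so much less.

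**Claims in favour of clonidine only.** With independent tests and k = 14, 1 − 0.975 × (1 − 0.025/14)^14 = 4.9%, against 2.5% for the primary alone. The ratio is about the same.

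**The two sections side by side.** Statistical analysis sets a significance level for an efficacy conclusion from a secondary endpoint alone. The Discussion says the sample cannot support conclusive results on secondary endpoints. This conflict needs no calculation.

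**The case against.** The strongest defence is that this is an exploratory trial. The Primary endpoint section speaks of exploring potential superiority, and the Secondary endpoints section presents the other outcomes as groundwork for a later, more definite study. The Bonferroni sentence is conditional, so it can be read as a restraint on secondary-only claims rather than a plan to make one. It does hold the secondary family at 5%, and the primary test keeps its own level. The Discussion sentence also sits in a paragraph that opens on delirium subtypes.

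Much of this stands, and it lowers the severity. It does not remove the point. Once the protocol sets a level for an efficacy conclusion, that level should hold for the trial's efficacy claims as a whole. The Discussion sentence is worded for secondary endpoints in general, not only for subtypes.

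The correlation argument also stands in part. The delirium endpoints measure much the same thing as the primary, so a reader who infers a flat doubling of the error rate goes too far. That is the independent or upper-bound case, and moderate correlation brings the rate to roughly 8–9%.

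A reader might also infer that "dividing the 5% level with the actual number of tests performed" inflates the error in itself. It does not: with independent tests the rate stays at 9.6–9.75% from k = 1 to k = 30. Harm would need a results-driven choice of which tests to run or count, and the document does not plan one.

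**Conclusion.** The rule is wrong as written and should be corrected. Under the global null, the chance of a false efficacy claim is up to 10%: 9.6–9.75% with independent tests, roughly 8–9% under moderate or mixed correlation, and near 5% only if the endpoints are almost perfectly correlated. The bound rests on the protocol's text alone. The figures below it rest on assumed correlations and on 14 tests, and they fall slightly if the primary is counted in the divisor. The conflict with the Discussion stands without any of these assumptions. The primary test itself is not affected.

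The point does not extend to the unadjusted secondaries after a positive primary. A reader might multiply out the 14 rows of Table 2, 1 − 0.95^14 = 51%, and read that as the trial's error rate. The documents do not support this. Some rows, such as serum drug concentrations, are not efficacy comparisons between arms, and the rows are unlikely to be independent. Under the global null this branch also adds no further false efficacy claim, because the significant primary has already made one. Unadjusted secondaries are ordinary practice when they are labelled exploratory, as the Discussion does.

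**What to change.** Delete the secondary-only route from Statistical analysis and replace it with wording such as: *If the MDAS comparison is not significant at the 5% level, no conclusion on efficacy will be drawn from any secondary endpoint. Secondary endpoints are exploratory and will be reported with estimates and 95% confidence intervals, whether or not the primary is significant.* This restores 5.0% and agrees with the Discussion. It costs a wording change, made before unblinding, and the option of claiming efficacy from a secondary alone, which the Discussion already disclaims.

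If the sponsor wants to keep the route, one overall 5% has to be shared between the primary and a fixed, pre-listed set of secondary tests. For example, 4% for MDAS and 1% divided among the listed secondaries gives at most 4% + 1% = 5%. Single-time MDAS power then falls from 79.3% to Φ(2.778 − 2.054) = 76.5%, that is, from about 79% to about 76–77%.
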